### Baseline data

2.9.

This study will collect descriptive data including gender, age, onset, weight, etiology etc. before randomization. The CRS-R was used to evaluate DoC’s consciousness level, and this will be applied initially to check if the three groups are the same prior to the intervention.

### Outcome measures

2.10.

The primary outcome for this study, coma recovery as measured by the Coma Recovery Scale-Revised (CRS-R), will be assessed at five time points for each period, ranging from the first to the fourth. This data will be used to determine the efficacy of the intervention being studied. The secondary outcomes of this study will be measured at both the baseline and the end of the fourth week of the study. Specifically, EEG, MRI, P-tau, and NFL will be used to measure these outcomes. These measurements will provide valuable insight into the effects of the study and help to further understand the results. Any detrimental outcomes or side effects will be noted during the course of the treatment.

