**Methods/design:**

Nighty patients with DoC acquired brain injury are randomized into one of three groups receiving sham taVNS or active taVNS (just left and left or right), respectively. Each of the three groups will experience a 40 days cycle (every 10 days for a small period, baseline 2 weeks, intervention 2 weeks, 40 min per day, 5 days per week, then no intervention for 2 weeks, intervention 2 weeks, 40 min per day, and 5 days per week). Primary outcomes (CRS-R) will be recorded five times during every period. Secondary outcomes will be recorded at the first and at the last period [MRI, EEG, Phosphorylated tau (P-tau), and Neurofilament light chain (NFL)]. We will take notes the adverse events and untoward effects during all cycles.

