### Study design

2.1.

Ninety patients suffering from DoC will be chosen for this prospective, randomized trial which involves double-blinded assessments. The participants will be randomly divided into the intervention and control groups with an even distribution. The control group will be administered ear lobe therapy, in contrast to the intervention group which will receive the active taVNS. We will stimulate left cymba conchae for one group, the second group subjects will be stimulated left cymba 20 min and right cymba 20 min once a day. Because we have not seen the side effects from the clinical practice, and the right vagus nerves modulate the left hemisphere. This study will last 40 days and a half-year observation period will follow. CRS-R behavioral improvement will be monitored five times every 10 days. At the beginning and the end of the fourth period, the following tests will be carried out: EEG, MRI, and measurement of certain biomarkers related to brain injuries. All side effects during each treatment will be documented. This study will be implemented in Shanghai Yongci Hospital, and rehabilitation therapists are held accountable for following the standard operating procedure and evaluating the trial’s progress at all clinical sites. This trial is illustrated in Figure 1.

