### Statistical analysis

2.13.

Main statistical analyses will be performed at the individual and group levels (pre vs. post, treatment vs. sham) (26). To examine the differences between the groups, we shall employ the *t*-test or Mann–Whitney test for continuous variables and the Pearson Chi-squared or Fisher’s exact test for discrete values. If a statistically significant result appears, the inequality factors will be considered as potential confounding factors in the final analysis of effectiveness. To account for any potential external influences, linear models or linear regression will be implemented on continuous dependent variables and logistic regression models on categorical dependent variables. The Chi-square test or Fisher’s exact test will be employed to document and assess unfavorable events (26). We will test outcomes on behavior (diagnosis, CRS-R score) and brain data (MRI/EEG). The proportion of responders and the effect size of treatment (*r*, Cohen’s *d*) will be calculated. We will use *t*-tests, Chi-square tests, ANOVA (for normally distributed data), and Wilcoxon test (for non-ordinal data), and mixed-effect regression models, depending on the tested outcomes. EEG and MRI analysis will be evaluated using SPM12 software^1^ and EEGLAB^2^ implemented in MATLAB 9.5 (MathWorks, Natick, MA, United States), respectively. All other statistical analyses will be conducted in SPSS software (version 25). All data will be adjusted to account for multiple comparisons and considered statistically significant if the value of *p* is lower than 0.05.

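### The primary CRS-R outcome covers four periods and three arms, but no period, summary of readings or arm contrast is fixed to decide efficacy

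*Protocol article*

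**What the plan says.** Section 2.10 (Outcome measures) says the CRS-R "will be assessed at five time points for each period, ranging from the first to the fourth", and continues: "This data will be used to determine the efficacy of the intervention being studied". The Abstract agrees ("Primary outcomes (CRS-R) will be recorded five times during every period"), and so does section 2.1 ("CRS-R behavioral improvement will be monitored five times every 10 days").

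The Abstract describes the cycle as "every 10 days for a small period, baseline 2 weeks, intervention 2 weeks, 40 min per day, 5 days per week, then no intervention for" two weeks, followed by a second intervention stretch. Periods 1 and 3 are therefore without stimulation. There are three arms, since patients are "randomized into one of three groups receiving sham taVNS or active taVNS (just left and left or right), respectively".

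Section 2.13 (Statistical analysis) names two kinds of main comparison, before versus after and treatment versus sham. It does not say which of the two active arms counts as treatment. It lists t-tests, chi-square tests, ANOVA, the Wilcoxon test and mixed-effect regression, with the choice depending on the outcome. Baseline variables enter the effectiveness analysis as confounders only if a group test on them is significant. On multiplicity it says: "All data will be adjusted to account for multiple comparisons and considered statistically significant if the value of *p* is lower than 0.05".

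**The concern.** A primary outcome should lead to one result that settles the efficacy question. Here the article states a primary outcome that cannot do so. It does not say which period counts, how five readings become one value, or which arms are compared. A before-after change within an active arm and a difference from sham answer different questions, and either could be presented as the main result.

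The multiplicity sentence does not close the gap, because it names neither a method nor a family of tests. If the family is chosen late, the choice can follow the data. If all data is taken literally, alpha is spread over every reading, arm pair and modality, and little power remains for the CRS-R.

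Adjusting for baseline only after a significant baseline test adds another data-dependent choice to the primary analysis.

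**Working it through.** **1. Does the sample size identify the deciding comparison?** Section 2.3 uses a paired formula with SD of the difference 15, difference 10, two-sided alpha 0.05 and 90% power:

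n = (1.960 + 1.282)² × 15² / 10² = 10.507 × 2.25 = 23.64, rounded up to 24.

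The stated 24 is reproduced, and 24/0.80 = 30 per group gives 90 in total. This is a within-patient calculation. A comparison of two arms with the same inputs would need 2 × 23.64 = 47.3, so 48 per arm. The sample size therefore does not point to an active-versus-sham contrast as the primary test.

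**2. Count of readings.** 5 readings × 4 periods = 20 (derived, not printed). Of these, 10 fall in periods 1 and 3, and 15 fall after baseline.

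**3. Two ways the CRS-R could be tested.**
- Milder reading: one score per post-baseline period and each active arm against sham, 3 × 2 = 6 tests.
- Worst case: every post-baseline reading and every arm pair, 15 × 3 = 45 tests.

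**4. Unadjusted family-wise error.** Simulated under no effect with 30 per arm, normal data, equal correlation between a patient's readings, and each test at 0.05. The correlations are assumed, as the article gives none.

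| Correlation | 6 tests | 45 tests |
|---|---|---|
| 0.7 | 19% | 51% |
| 0.8 | 18% | 42% |
| 0.9 | 15% | 32% |

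**5. Power of one active-versus-sham test.** Two-sample t-test with noncentrality (10/15) × √(n/2), which is 2.58 at n = 30 and 2.31 at n = 24. This assumes that the paired 10/15 effect applies between arms.

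| Tests sharing alpha | Alpha per test | Power, 30 per arm | Power, 24 evaluable |
|---|---|---|---|
| 2 | 0.025 | 61% | 50% |
| 6 | 0.0083 | 45% | 34% |
| 45 | 0.0011 | 21% | 14% |

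These are powers for a single named test at the Bonferroni level, not the chance that at least one of the tests succeeds.

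**The case against.** Several stronger readings are tempting, and the article does not support them.

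- **That the CRS-R is tested only with two-group tests in a three-arm trial.** The sentence naming the t-test or "Mann–Whitney test for continuous variables" is followed at once by the rule that unequal factors become confounders. It reads largely as a baseline-balance check, in line with section 2.9. Section 2.13 also lists ANOVA and mixed models, which can handle three arms. The fault is that none of these is tied to the CRS-R.
- **That the effect is diluted by averaging over untreated periods.** Nothing in the article plans to average the four periods. Period 1 may well be meant as the before value, though this is not said.
- **That 45 separate tests are planned.** They are not. Section 2.2 uses five CRS-R assessments to establish a patient's diagnosis, so five readings per period may be repeats meant to give one score. This is why the 6-test reading is shown first.
- **That error is uncontrolled.** Some adjustment is promised, so the unadjusted rates are upper scenarios and do not describe the plan.

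It can also be said that the adjustment method and the summary of repeated readings usually belong in the analysis plan, which is not at hand. That is fair for the technical detail. It does not cover the endpoint itself: the article states a primary outcome and says how it will be used, and that statement gives no single verdict. Choosing period 4 or the mean is a design preference. Choosing something is not.

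**Conclusion.** The point holds. The primary outcome as stated in 2.10, read with 2.13, leaves the deciding period, the summary of readings, the arm contrast and the method open, and the multiplicity sentence does not resolve them.

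On the milder reading, leaving this open would allow a family-wise error of about 15–19% if no adjustment were applied. Bonferroni over the same six tests gives about 45% power per test. The worst case is about 32–51% and 21%. Restricting alpha to two active-versus-sham contrasts gives about 61%, or 50% with 24 evaluable per arm.

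These sizes rest on assumed correlations of 0.7 to 0.9 and on using the paired 10/15 effect between arms. They illustrate the cost and are not properties of a stated analysis. That the endpoint is not fixed does not depend on them.

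**What to change.** In 2.10, name one primary CRS-R endpoint, for example the mean of the five period-4 readings. In 2.13:

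- Use the period-1 CRS-R summary as a covariate whatever any baseline test shows.
- Compare each active arm with sham from one three-arm ANCOVA, or a mixed model using all periods.
- Apply Holm or Dunnett control over these two contrasts only.
- Label left versus bilateral, before-after change, other periods, EEG, MRI and biomarkers as secondary, and state how multiplicity is handled there.

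The periods must first be unambiguous. The Abstract gives both 10-day periods in a 40-day cycle and two-week stretches, and 4 × 14 = 56 days does not fit 40. These statements need to be reconciled.

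The cost is wording, with no new data. Enrolment began in April 2021, and section 2.6 speaks of the trial as already concluded while the trial status section expects it to end by December 2023. The change should therefore be dated, documented and made before the first unblinding step in section 2.7. Other time points and contrasts lose primary status. The change does not restore 90% power: about 61% remains on the assumptions above, before any gain from the baseline covariate, which the article gives no figure to size.

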### Primary outcomes

2.11.

#### Coma recovery scale-revised

2.11.1.

The CRS-R is used to measure the progress of individuals suffering from DoC (UWS,MCS−, and MCS+) (7). The CRS-R is made up of 23 components organized into six sections that evaluate auditory, visual, motor, oromotor, communication, and arousal functions. Scores that are higher indicate conscious-related behavior, while lower scores signify reflexive activity. The evaluation of performance is dependent on the occurrence or lack of the specified action in response to standard prompts (14).

### Secondary outcomes

2.12.

#### Electrophysiology

2.12.1.

The benchmark for assessing levels of consciousness is the CRS-R (15, 16), whereas EEG is a crucial diagnostic and prognostic tool for patients with DoC (17). Recent advancements in the field have enabled researchers to develop feature-based measures like spectral power analysis, functional connectivity, and complexity measures, for the purpose of diagnosing and predicting outcomes (18–20). Despite this, their use to assess the efficacy of treatments has not been implemented (More EEG details are shown in Supplementary material). In this study, we would analyze spectral power analysis mostly to identify an improvement on EEG (such as alpha power) (17).

#### Magnetic resonance imaging

2.12.2.

In this study, rest Fmri research must always include a brainstem assessment in order to verify the Vagal Cortical Pathways model’s pathways. This can be confidently relied upon as a guarantee of quality in taVNS studies, as it clearly demonstrates the stimulation of the vagus nerve (4). Furthermore, subcortical regions like the thalamus and striatum should be taken into account. Brain connectivity can be estimated by utilizing the thalamus, frontal lateral cortex, anterior cingulate cortex, insula, and posterior cingulate cortex as seed regions in Fmri studies. Moreover, measuring brain activity during tasks should be the preferred approach (21, 22). In severe TBI, an increase in fractional anisotropy (FA) on the initial postinjury diffusion tensor imaging (DTI) was associated with a favorable outcome, and these results suggest that it is secondary to axonal regrowth during later recovery. A variety of other cognitive and functional outcomes in mild to severe TBI have been correlated to DTI (23). Finally, DTI-FA should be analyzed in our study (More MRI details are shown in Supplementary material).

#### Single-molecule Array

2.12.3.

The peripheral blood will be taken regularly according to the experimental protocol, imaging samples will be selected, and the target protein determination will be performed using Simoa HD-1 (Single-Molecule Array Analyzer), known as the digital ELISA with more than 1,000 times higher sensitivity than conventional ELISA (24).

The enrolled subjects will be collected peripheral venous blood before and after the taVNS intervention. Samples with obvious imaging effects will be selected, and the target protein (p-tau, NFL) will be determined using Simoa HD-1 Analyzer to explore whether the target protein levels changed before and after taVNS intervention and whether this change is correlated with consciousness (25).

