### Randomization

2.4.

The study will utilize block randomization. The participants will be classified into either the “MCS group” or the “UWS/*VS* group.” All subjects will be randomly divided into the intervention group and control group in a 1:1:1 ratio. To ensure impartiality, a random number will be used to produce a random allocation order, this task will be handled by a person who is not involved in the trial. The order of random allocation will remain undisclosed to those assessing the outcomes and the statistician. After evaluating the baseline information of the suitable participants, their healthcare personals and therapists (including acupuncturists and cognitive therapists) will not know patients random number assigned.

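### P-tau and NFL are to be assayed only in samples chosen on an undefined imaging effect seen after treatment begins, which conflicts with their listing as secondary outcomes and can bias the biomarker results

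*Protocol article*

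**What the plan says.** Section 2.10 (Outcome measures) names the proteins among the secondary outcomes: "Specifically, EEG, MRI, P-tau, and NFL will be used to measure these outcomes". It says that the secondary outcomes "will be measured at both the baseline and the end of the fourth week of the study". The Abstract lists P-tau and NFL in the same way. Neither place mentions a subset.

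Section 2.12.3 (Single-molecule Array) collects blood broadly: "The enrolled subjects will be collected peripheral venous blood before and after the taVNS intervention". It then restricts the assay. Its first paragraph says "imaging samples will be selected, and the target protein determination will be performed using Simoa HD-1", and its second says "Samples with obvious imaging effects will be selected, and the target protein (p-tau, NFL) will be determined using Simoa HD-1 Analyzer". The purpose given is "to explore whether the target protein levels changed before and after taVNS intervention and whether this change is correlated with consciousness".

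Section 2.13 (Statistical analysis) plans both kinds of comparison: "Main statistical analyses will be performed at the individual and group levels (pre vs. post, treatment vs. sham". Section 2.4 (Randomization) sets the allocation: "All subjects will be randomly divided into the intervention group and control group in a 1:1:1 ratio".

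No threshold, imaging modality, direction of effect, reader or number of samples is given for the selection.

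**The concern.** An effect on imaging can be judged only by comparing a later scan with the baseline scan, so it is known only after randomisation and after treatment has started. Selecting samples on it means selecting on a post-randomisation outcome. The protocol itself treats imaging as related to recovery: section 2.12.2 links an increase in fractional anisotropy to favourable outcome.

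Three things are at stake.

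- **The pre-post question.** If patients whose scans improved are kept, and imaging change tracks protein change, the assayed group can show a mean protein change that the whole cohort does not have.
- **The comparison with sham.** If taVNS alters imaging, the arms pass the filter differently and the selected groups are no longer comparable.
- **The correlation with consciousness.** It would be estimated in a sample filtered on a variable thought to be related to recovery. This may alter the correlation; I put no size on it.

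The Introduction makes identifying biomarkers and therapeutic targets the third aim, and that aim relies on these assays. Because this is a stated rule about which samples are assayed, a later analysis plan could not recover data that were never generated.

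**Working it through.** **The plan's own figures.** There is no sample size or effect size for the biomarkers. The only sizing is for CRS-R (section 2.3): n = (1.960 + 1.282)² × 15² / 10² = 23.6, rounded up to 24, as stated. The plan raises this to 30 per group and 90 in total. The point does not depend on this calculation; it only uses the total of 90.

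**Inputs.** From the document: 90 patients, three equal arms, and pre-post and active-versus-sham comparisons. Assumed, because the document gives none of them: the correlation ρ between imaging change and biomarker change, the fraction q assayed, and the direction of selection.

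**Check 1: pre-post change when taVNS does nothing.** Imaging change and biomarker change are bivariate normal with mean 0, SD 1 and correlation ρ. The top fraction q by imaging change is assayed, and a one-sample t-test is applied to biomarker change (20,000 simulated trials).

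The expected mean in the selected group is ρ × φ(z₁₋q) / q. With q = 1/3, z = 0.431 and φ(z) = 0.364, so the multiplier is 0.364 / 0.333 = 1.09. That gives about 0.22 SD at ρ = 0.2, 0.33 at 0.3 and 0.55 at 0.5. The simulated values for 30 of 90 agree closely:

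| ρ | Bias (SD), top 30 of 90 | False positives, top 30 | False positives, top 45 | False positives, top 18 |
|---|---|---|---|---|
| 0 | 0.00 | 5.0% | 4.7% | 5.1% |
| 0.2 | 0.22 | 21.5% | 18.5% | 20.2% |
| 0.3 | 0.32 | 42.5% | 36.8% | 40.6% |
| 0.5 | 0.54 | 87.6% | 80.3% | 86.5% |

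The fraction assayed matters little; the correlation matters a great deal. With all 90 assayed, the bias is 0.00 SD and the false-positive rate is 4.6% to 5.1% at every ρ from 0 to 0.7.

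**Check 2: direction.** If the 30 largest absolute imaging changes are taken instead, the bias is 0.00 SD by symmetry and the false-positive rate is 4.6% to 5.4% for ρ from 0 to 0.5.

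**Check 3: active versus sham when taVNS does nothing.** In the simulations of Check 1, the two-sample test within the selected patients rejects in 4.7% to 5.2% of trials. Selection acts alike in every arm, so the error rate holds.

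**Check 4: active versus sham when taVNS shifts imaging but not the biomarker.** Samples are assayed if imaging change exceeds 0.5 SD (assumed). The mean biomarker change among those selected is ρ × φ(c) / (1 − Φ(c)), where c is 0.5 in sham and 0.5 minus the imaging shift in the active arms.

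- Sham, c = 0.5: 0.352 / 0.309 = 1.14, so 0.34 SD at ρ = 0.3 and 0.57 SD at ρ = 0.5.
- Active, shift 0.5, c = 0: 0.399 / 0.500 = 0.80, so 0.24 and 0.40 SD. Active minus sham is -0.10 and -0.17 SD.
- Active, shift 1.0, c = -0.5: 0.352 / 0.691 = 0.51, so 0.15 and 0.25 SD. Active minus sham is -0.19 and -0.32 SD.

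Simulation gave the same differences. At ρ = 0 the difference is zero. The filter keeps 31% of sham patients, against 50% or 69% of active patients, so the groups compared are selected differently.

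**The case against.** **The harm is conditional.** Selection alone does not create a change. It needs a non-zero correlation, which the document does not give, and a filter that favours one direction, which the wording does not specify. This stands in full. A reader might infer that the assay will show change even if taVNS does nothing, or that the randomised comparison is lost in every case. The documents support neither. With ρ = 0 or two-sided selection there is no bias, and if taVNS does nothing the sham contrast keeps its nominal error. A non-zero correlation is still plausible, because the protocol's rationale supposes that imaging, proteins and consciousness move together.

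**The wording is loose.** The first mention of selection could mean only that patients with scans are used. That is fair for the first sentence. The second speaks of effects, not of scan availability or quality. If availability was meant, the sentence needs correcting all the same.

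**The assay is exploratory.** The section says that its purpose is to explore, section 2.13 names behaviour and MRI/EEG as the tested outcomes without mentioning the proteins, and CRS-R, MRI and EEG are unaffected. This lowers the severity. It does not remove the conflict with section 2.10 and the Abstract, or the third aim's reliance on these assays.

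**Conclusion.** The concern holds in a conditional form. Section 2.12.3 restricts a listed secondary outcome by an undefined criterion that is known only after randomisation and the start of treatment, and so conflicts with section 2.10 and the Abstract. That much rests on the text alone.

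The statistical consequence depends on assumptions. The uncontrolled pre-post result is biased only if imaging and biomarker changes correlate and selection is one-directional; the false-positive rate then runs from nominal up to nearly 90% over the correlations examined. The sham contrast is biased only if taVNS affects imaging and the correlation is non-zero; in the scenarios examined it was shifted by a tenth to a third of an SD, against the active arms in the direction of the imaging change. These figures show what the rule can do and do not predict what this trial will find.

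This should be fixed. It is not a threat to the primary analysis.

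**What to change.** Delete the imaging-based selection from both paragraphs of section 2.12.3 and bring the section into line with section 2.10 and the Abstract. Assay the baseline and end-of-treatment samples of every randomised patient who has both. If the assay budget does not allow this, assay a subset of the size now intended, drawn at random within arm and MCS/UWS stratum by someone blind to MRI, EEG and CRS-R results. Compare by randomised arm, adjusted for the baseline biomarker value.

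**Cost.** Blood is already to be taken from enrolled subjects before and after the intervention. Assaying everyone means up to about 90 × 2 = 180 samples for two proteins. This does not count the further blood draws for target proteins in section 2.6 (Follow-up). A random subset of the intended size needs no extra assays; its drawback is a smaller sample than assaying everyone.
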